**Session 2: Consequences and common triggers of IPV during pregnancy**

1. **Session 2 is provided in the second contact**
2. **Suggested time: 60 minutes**
3. **Session objective**

- To describe adverse maternal and new-born consequences of IPV during pregnancy
- To explain economic and social consequences of IPV during pregnancy
- To identify common triggers of IPV
- To state the ways to challenge triggers of IPV

1. **Activity**

**Steps**

1. Warmly welcome the couples to the 2^nd^ education session
2. Reflections on take home exercises with the couples
3. Introduce the session: today we will begin on maternal, social and economic consequences of IPV and common triggers of IPV will be here to guide the lecture. However, your participation will also propel us forward. Your contributions are what will enrich this session and give it meaning in your lives.
4. Prepare materials like note book and pen
5. Start the teaching on the given topic
6. Give time for questions or ask questions whether the couples understand or not

- Make sure that the couples responded at least 75 percent of the questions asked
- If the couples do not respond at least 75 percent of questions raised by the trainer, repeat the session for another time.

1. Introduce the take home exercise, appointment for next session and acknowledge couples for the their participation

**Session 3:**

**Provide the session three at third contact**

1. **Suggested time: 45 minutes**
2. **Session objectives**

- To enable the couples on pregnancy related consequences of violence during pregnancy

1. **Activity**

**Steps**

1. Warmly welcome the couples to the 3^rd^ education session
2. Reflections on take home exercises with the couples
3. Introduce the session: today we will continue on pregnancy-related consequences of violence during pregnancy. Furthermore, your participation has a paramount role in the success of this session.
4. Prepare materials like note book, pen and posters
5. Start the teaching on the given topic

- Pregnancy related consequences of violence

Direct and indirect effect

- Effect of violence on perpetrators
- Effect of violence on society

1. Importance of male involvement in maternal health care
2. Give time for questions or ask questions whether the couples understand or not

- Make sure that the couples responded at least 75 percent of the questions asked
- If the couples do not respond at least 75 percent of questions raised by the trainer, repeat the session for another time.

1. Introduce the take home exercise and appointment for next session, acknowledge the participants

**Session4: power, control and intimate partner violence**

1. **Provide this session at fourth contact**
2. **Suggested time: 45 minutes.**
3. **Session objectives:**

- To enable the couples with power and control balance in relationship
- To enable the couples with a healthy power balance in relationship of couples
- To discuss the role of male partners during pregnancy

1. **Activities**

**Steps**

1. Warmly welcome the couples to the 4^th^ education session
2. Reflections on take home exercises with the couples
3. Introduce the session: today we will continue on power and control balance in relationship, how to have a healthy relationship among couples, and the role of male partners during pregnancy. Again, your participation is crucial in this session.
4. Prepare the quite place for lecture, materials like note book and pen
5. Start the teaching on the given topic

- Power and control balance in relationship
- How to have a healthy relationship among couples
- Role of male partners during pregnancy

1. Continue to lecture
2. Give time for questions or ask questions whether the couples understand or not

- Make sure that the couples responded at least 75 percent of the questions asked
- If the couples do not respond at least 75 percent of questions raised by the trainer, repeat the session for another time.

1. Introduce the take home exercise, appointment for next session and acknowledge the participants

**Session 5: triggers of IPV**

1. **Provide this session at fifth contact**
2. **Suggested time: 40 minutes**
3. **Objectives of the session**

- To discuss a health relationship in marital union
- To discuss the power and control balance in relationship
- To elaborate the roles of males during pregnancy

1. **Activity**

**Steps**

1. Warmly welcome the couples to the 5^th^ education session.
2. Reflections on take home exercises with the couples
3. Introduce the session: today we will continue on common triggers and methods of women empowerment. Furthermore, your participation has paramount role for the success of this session.
4. Prepare the quite place for lecture, materials like note book and pen
5. Start the teaching on the given topic

- Common triggers of IPV during pregnancy
- A healthy relationship in marriage
- The roles of male partners during pregnancy

1. Give time for questions or ask questions whether the couples understand or not

- Make sure that the couples responded at least 75 percent of the questions asked
- If the couples do not respond at least 75 percent of questions raised by the trainer, repeat the session for another time

**Session six 6: women empowerment**

1. **Provide this session at sixth contact**
2. **Suggested time: 40 minutes**
3. **Objectives of the session**

- To be familiar with the concepts of women empowerment with the couples
- To enrich the couples with the importance of women empowerment in prevention of IPV in pregnancy

1. **Activity**

**Steps**

1. Warmly welcome the couples to the 6^th^ education session.
2. Reflections on take home exercises with the couples
3. Introduce the session: today we will continue on women empowerment and of women empowerment. Furthermore, your participation has paramount role for the success of this session.
4. Prepare the quite place for lecture, materials like note book and pen
5. Start the teaching on the given topic

- Women empowerment
- Importance of women empowerment in IPV during pregnancy

1. Give time for questions or ask questions whether the couples understand or not

- Make sure that the couples responded at least 75 percent of the questions asked
- If the couples do not respond at least 75 percent of questions raised by the trainer, repeat the session for another time

1. Close up

Feedback from the couples

Acknowledge the couples

**The end!**

**Annex-V: Handout for Couple Based Violence Prevention Education (CBVPE)**

**Gender Based Violence (GBV)**

- Gender based Violence: refers to all forms of violence that happen to women, girls, men, and boys.
- It occurs due to unequal power relations between the victim and perpetrators.

**Violence against Women (VAW)**

- Violence against Women(VAW) is any act of gender-based violence that results in
  - - physical,
    - sexual,
    - psychological harm
    - suffering ,
    - threats ( acts, coercion, or arbitrary deprivations of liberty) to women
- It can be occurred in public or private life.

**Intimate Partner Violence (IPV)**

Intimate partner violence (IPV) refers any behavior within an intimate relationship that causes physical, psychological or sexual harm to the partner.

Intimate partner violence accounts for the lion share of Violence against Women.

Intimate partner violence occurs in the form of

- Physical,
- Sexual,
- Psychological or emotional,

**Physical intimate partner violence (IPPV) includes**

- Slap you or throw something that could hurt the partner
- Push the partner,
- Punch in abdomen
- Kick in abdomen
- shove the partner or pull the hair of the partner,
- Hit with his fist or with something else that could hurt the partner
- Kick ,
- Drag about or beat the partner up
- Attempt to choke or burn on purpose
- Threaten to use or actually use a gun, knife or other weapon against the partner

**Sexual Intimate Partner Violence (SIPV) includes**

- Physically force the partner to have sexual intercourse when she/he did not want to or
- Force the partner with threats or in any other way to perform sexual acts she/he did not or want
- Physically force the partner to perform any other sexual acts she /he did not want to

**Psychological or emotional Intimate Partner Violence (SEIPV) includes**

- The partner says or does something to humiliate her/him in front of another person or
- Threaten to hurt or harm her/him or someone she/he care about or
- Insult her him or make she/he feel bad about her/himself

**Magnitude of Intimate Partner violence (IPV)**

- Each year, between 1.5 and 5.3 million women are physically and/or sexually assaulted by an intimate partner.
- In Ethiopia, studies indicate that pregnancy intimate partner violence in pregnancy ranges from 26%-65%

**Session 2**

**Consequences of Intimate partner violence in pregnancy**

**Maternal health consequences**

***Physical***

- Injury(broken bone, burns, cuts, broken teeth, broken hands and legs)
- Physical impairment
- Lack of attachment to child
- Sexual and reproductive health problems(contracting sexually transmitted diseases, spread of HIV/AIDS, high-risk pregnancies, etc)
- Disability
- Homicide
- Antepartum hemorrhage
- Maternal death

***Psychological***

***Direct effect: anxiety, fear, mistrust of others, inability to concentrate, loneness,*** post-traumatic stress disorder, depression, homicide, suicide, etc.

***Behavioral***

- Multiple sexual partners
- Alcohol use during pregnancy
- Smoking during pregnancy
- Chat chewing
- Delayed antenatal care use

***Economic and social consequences***

- Rejection, ostracism, and social stigma at community level
- Reduced ability to participate in social and economic activities
- Acute fear of future violence, which extends beyond the individual survivors to other members in community
- Damage to women’s confidence resulting in fear of venturing into public spaces
- Increased vulnerability to other types of gender-based violence
- Job loss due to absenteeism as a result of violence
- Negative impact on women’s income generating power

***The impact on women’s family and dependents***

- Divorce, or broken families,
- Jeopardized family’s economic and emotional development ¸
- Premature birth or low birth weight
- Increased likelihood of violence against children growing up in households where there is domestic violence

**Session -3**

**Pregnancy consequences (adverse pregnancy outcomes)**

- Increased risk of intrauterine growth retardation
- Increased risk of preterm labour
- Increased risk of miscarriage
- Increased risk of unsafe abortion
- Increased risk of still birth
- Increased risk of perinatal death
- Low-birth weight
- Insufficient weight gain
- STI/HIV
- Neonatal death

***The impact of violence on perpetrators***

- Sanctioning by community
- Facing arrest and imprisonment
- Legal restrictions on seeing their families
- Divorce or the breakup of their families
- Feeling of alienation from their families
- Minimizing the significance of violence for which they are responsible
- Deflecting the responsibility for violence onto their partner and failure to associate it with their relationship
- Increased tension in the home

***The impact of violence on society***

- Burden on health and judicial systems
- Hindrance to economic stability and growth through women’s lost productivity
- Hindrance to women’s participation in the development processes and lessening of their contribution to social and economic development
- Constrained ability of women to respond to rapid social, political, or economic change
- Breakdown of trust in social relationships
- Weakened support networks on which people’s survival strategies depend.
- Strained and fragmented networks that are of vital importance in strengthening the capabilities of communities in times of stress and upheaval

**Importance of male involvement in maternal health care (Antenatal, delivery and postnatal)**

- Gets information on importance of antenatal care, facility delivery and postnatal check -up) from health care providers
- Reminds the partner (his wife) to antenatal appointments
- Arranges the transportation including money to go hospital or health center for antenatal check-up
- Yield benefits relating to maternal workload during pregnancy,
- Enables the couples ready for birth preparedness and complication readiness,
- Postnatal care attendance,
- Enables husbands communication and emotional support for women during pregnancy
- Improve child feeding practice including exclusive breast feeding
- Improves child immunization coverage
- Improves contraceptive use after child birth

Take-home exercise

Who make the final decision in the following activities?

- Household purchases including small and large ones,
- Visiting relatives and friends
- Spending the wife's earnings
- The number of children to have
- Obtaining health care for yourself

**Session-4**

***Power in relationships***

- Power in relationship enables the couples to control, make choices ,and have the capacity to impact the current circumstances
- A lack of power is a constant reminder of not being in control of our decisions or our destiny.

**Shared power**

- Occurs when partners are aware and confident about their self-worth and autonomy

**Power affects the relationship**

- In relationships that are strong and healthy, the influence both partners have is almost equal.
- One might have more financial power, the other more social connections, but ultimately they are respectful of one another and make decisions together

**Effects of imbalance of power in relationship**

- Damaged intimacy and relationship
- Intimate partner physical, sexual and psychological violence
- Frustration, anger, and depression
- Feelings of anxiety, fear and shame
- Impaired self-esteem, self-image and sense of person value
- Isolation, threats and abuse
- Lack of trust in the partner and endurance of the relationship
- Decreased overall satisfaction of the relationship
- End of relationship or marriage

**How to have healthy power balance in relationship of couples**

1. **Respect each other**

- Respect and trust are the foundations of any strong relationship
- Respect the views of your partner

1. **Make Money decisions together**

- Most of the time, the power balance in relationship is determined by money.
- Couples decide money expenditure together

1. **Develop good communication**

- One of the hallmarks of unhealthy or imbalanced power dynamics in relationship is lack of communication between couples.
- Both partners should have the freedom to address issues without fear
- Freedom to speak your mind is the key to a healthy relationship

1. **Increase your self-confidence**

- Lack of confidence or low self-esteem of one of the partners leads to power imbalance
- Work on your self-first
- Develop a healthy relationship with yourself,
- Learn to communicate your needs clearly and effectively

1. **Couples strive to meet relationship needs**

- Relationships are all bout give and take
- Realizing your own power as well as your partner one is key to a balanced and health relationship

**Role of husband/male partner during pregnancy**

“Pregnancy is a life changing phase for every woman”

“A wife supported by her husband will feel happier and less stressed”

1. **Accompany your wife during all medical appointments**

- Antenatal care
- During delivery
- Postnatal check-up
- Any medical check-up
- This allows the partner to follow the health condition of his wife and his baby
- Strengthen the emotional support for the women

1. **Participate in household chores**

- Understand that your wife is going through a transformation process that she needs
  - Rest
  - Support
  - Lots of understanding

1. **Communicate with your wife/partner**

- Very helpful to identify any anxiety that she has
- Opens the door to support your wife

1. **Prepare a birth plan**

- Financial preparation
- Prepare for transportation
- Plan for where to give birth

1. **Understand her moodiness**

- Hormonal changes in pregnancy may make moody due to discomfort, exhaustion and tiredness
- She may be happy at one second, may be any at another time
- Understand her moodiness

1. **Take care of her diet**

- You have to make sure that your wife is getting adequate nutrition.
- Encourage to eat more healthy food

1. **Get her enough sleep and rest**
2. **Become a good listener of your wife**
3. **Make change in your lifestyle**

- Avoid drinking too much coffee
- stop or avoid smoking around your pregnant wife
- Avoid drinking liquor

1. **Plan for walks**

Takes-home exercise

- What triggers of intimate partner violence during pregnancy in your family?
- How do you solve when disagreement appears in your relationship

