**6.15 Description of the Intervention**

The purpose of the study is to provide community-based health education to couples on violence prevention to reduce intimate partner violence during pregnancy. A group health education on violence prevention, including intimate partner violence, for couples in the intervention group will be provided in a place center for the participants. 16 kebels found in the four districts will be the study clusters.

A package of health education messages on violence prevention will be provided to couples living in the intervention arm. The package was adapted from a psychosocial education study conducted among couples (Mutisya et al., 2018) and gender transpormative education on intimate partner violence in Tanzania (Harvey et al., 2021). The health education messages will be conducted by health extension workers who are working in intervention clusters (kebeles). Eight health extension workers will be selected for the intervention (CBVP education). The following criteria will be used to recruit health extension workers:

- Health Extension Workers who are female
- able to speak Amharic and the local language (Hadiyisa).
- willing to participate in the study period
- Good interpersonal and communication skills
- Having participated in a survey previously

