**6.24 Ethical Consideration**

Ethical approval of the study will be obtained from the Ethical Review Board of Jimma University. Then, permission letter to precede the study will be obtained Regional health Bureau and Zonal Health department. The research participants will be enrolled into the study after informed verbal and written consent is obtained. Confidentiality of the respondents will also be maintained. The purpose of the study and the right of the respondent not to participate and not to answer the question for which she didn't want to will be explained carefully to respondents before asking informed and written consent to conduct interview. All interviews will be taken place privately at place and time chosen by the respondent. Strict confidentiality will be assured through anonymous recording and coding of questionnaire and placing it in a safe place after they have been collected. For qualitative study, the interview will be carried out in a private place for the purpose of concentration and privacy of participants. Permission to use a tape recorder will be obtained from the participants prior to the interview for all qualitative study participants.

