**Couples take- home exercises and reflections**

All sessions contain take-home exercises that are assigned at the end of the session, and to help the couples reflect upon and apply new ideas in their own lives. Research shows that doing exercises at home following training significantly increases the effectiveness of the program. Each session, likewise, starts with a reflection of the take-Home exercise. The format of this reflection is the same for each session, with different guiding questions to facilitate debriefs.

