**እርግዝና ወቅት የባል/የወንድ አጋር ሚና**

**"እርግዝና ለእያንዳንዱ ሴት ሕይወትን የሚለውጥ ደረጃ ነው"**

**" ሚስት በባልዋ የምትደገፍ ሴት ደስተኛ ትሆናለች እና ጭንቀት ይቀንሳል"”**

1. **በሁሉም የሕክምና ቀጠሮዎች ጊዜ ከሚስትዎ ጋር አብረው መሄድ**

- የቅድመ ወሊድ እንክብካቤ
- በወሊድ ጊዜ
- የድህረ ወሊድ ምርመራ አብሮ መሔድ
- ይህም ባልደረባው የሚስቱን እና የልጁን የጤና ሁኔታ እንዲከታተል ያስችለዋል,
- ለሴቶች የሚሰጠውን ስሜታዊ ድጋፍ ማጠናከር

1. **በቤት ውስጥ ሥራዎች ውስጥ መሳተፍ**

- ሚስትህ በምትፈልገው የለውጥ ሂደት ውስጥ እንደምትገኝ ተረዳ

እረፍት

ድጋፍ

ብዙ ግንዛቤ

1. **ከባለቤትዎ/ባልደረባዎ ጋር መነጋጋር**

- እሷ ያለባትን ማንኛውንም ጭንቀት ለመለየት በጣም ጠቃሚ ነው ሚስትዎን ለመደገፍ በር ይከፍታል

1. **የልደት እቅድ ያዘጋጁ**

- የገንዘብ ዝግጅት
- ለመጓጓዣ ተዘጋጁ
- ወዴት እንደሚወልዱ ያቅዱ

1. **የሚስትን ስሜት መረዳት**

- በእርግዝና ወቅት የሚደረጉ የሆርሞን ለውጦች ምቾት ማጣት፣ ድካም እና ድካም ስሜት ሊሰማቸው ይችላል፣
- አንድ ሰከንድ ላይ ደስተኛ ልትሆን ትችላለች፣ በሌላ ጊዜም ቢሆን ምናልባት ስሜቷን መረዳት ።

1. አመጋገቧን ማስተካከል

- በቂ ምግብ እየተመገበች እንደሆነ ማረጋገጥ
- ጤናማ የሆኑ ምግቦችን እንድትጠቀም ማበረታታት

1. **በቂ እረፍትና እንቅልፍ እነድቶስድ ማድረግ**
2. **ምስትህን ደንብ ማዳመጥ**
3. **አኗኗሯን ማስተካካል**

- በጣም ብዙ ቡና እንደትጠጣ መከልከል
- በአጠገቧ አላማጫስ
- አስካሪ መጠጥ አለመዉሰድ

1. **የተወሰነ እግር ጉዞ እንደ መዝናኛ መሄድ**

የቤት ስራ/ተወያዩ

- የቅርብ አጋር ጥቃትን በእርግዝና ወቅት የሚያበባብሱ ነገሮች ምንድናቸዉ?
- በቤት ዉስጥ አላመግበባት ብፈጠር እንዴት ትፈታላችሁ?

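### The English take-home exercise asks couples what triggers violence in their own family and is then taken up in group sessions; the Amharic item is general, and no rule covers disclosure in the group

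*Protocol*

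**What the plan says.** **English handout (Annex V, end of the material on the husband's role in pregnancy).** The take-home exercise has two items: "What triggers of intimate partner violence during pregnancy in your family" and "How do you solve when disagreement appears in your relationship". Both are addressed to the couple about their own life together.

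**Amharic handout (Annex IX, same place).** The first item reads "የቅርብ አጋር ጥቃትን በእርግዝና ወቅት የሚያበባብሱ ነገሮች ምንድናቸዉ". In my translation, it asks what things aggravate intimate partner violence during pregnancy; the couple's family is not mentioned. The second reads "በቤት ዉስጥ አላመግበባት ብፈጠር እንዴት ትፈታላችሁ", that is, how the couple would settle a disagreement if one arose at home.

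**Use of the exercise (Appendix IV, trainers' manual).** The section on take-home exercises states: "Each session, likewise, starts with a reflection of the take-Home exercise". The second step of the next contact, session 5 on triggers, is "Reflections on take home exercises with the couples".

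**Setting.** Section 6.15 states: "A group health education on violence prevention, including intimate partner violence, for couples in the intervention group will be provided". Sections 6.15.1 and 6.15.2 and the manual's paragraph on participants confirm group teaching at a health post or health centre. Section 6.9 describes 27 pregnant women with their husbands in each kebele.

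**Language.** The English manual provides for Amharic or Hadiyisa according to preference. The Amharic manual (Annex VIII) names Amharic only.

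**Privacy.** Section 6.24 (Ethical Consideration) says "Confidentiality of the respondents will also be maintained" and provides for private interviews.

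**The concern.** The English item takes it for granted that there is violence in the couple's home to explain. As homework between two partners this is already delicate. It becomes more so when the next session opens with reflection on that homework, in a group that includes the husband and other couples from the same kebele.

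The protocol is otherwise careful about disclosure. Its background section says that many victims do not reveal violence. The women's questionnaire (Annex II) lists fear, and shame and embarrassment, among the reasons for having done nothing. Section 6.18 uses female interviewers to encourage disclosure. A personal question carried into a mixed group sits badly with that approach.

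What is at stake is first the safety of women in the intervention arm. There is also a question of consistency: one intervention item exists in two forms with different content, so the protocol does not settle which form is delivered.

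**Working it through.** No arithmetic applies. The check sets the texts side by side and follows the exercise from handout to session.

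1. **Item 1, English against Amharic.** The English places the question in the couple's own family. The Amharic asks about aggravating factors in general. These are different questions.
2. **Item 2, English against Amharic.** Both concern the couple's own home. The Amharic is conditional (if a disagreement arose); the English is not. The mismatch that matters is therefore in item 1 only.
3. **What happens to the answers.** The manual has the exercise taken up at the start of the next session, with guiding questions for a debrief. The step list for session 5 repeats this. The Amharic timetable in Annex VIII gives 10 minutes of session 5 to homework feedback.
4. **Who is present.** The sessions are for couples and are taught in groups, so husbands and other couples of the kebele are in the room. The size of a teaching group is not stated.
5. **Which wording is used.** Teaching is in Amharic or Hadiyisa. The Amharic item is general. No Hadiyisa handout is at hand, and nothing says whether one would be made from the English or the Amharic text.
6. **What protects a woman in the session.** Section 6.24 on ethics protects interviews. The section on appointment and follow-up has the health extension worker ask either partner each month about disputes due to the intervention, and negotiate if there are any. That finds trouble after it has occurred; it sets no rule for what couples are asked in the group. I find no such rule elsewhere.

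Points 1 and 5 establish an unresolved difference in content. Points 3, 4 and 6 show that, if the personal wording were used, it would reach a group setting without a disclosure rule.

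**The case against.** The strongest reply is that the English line is not shown to reach any couple. Sessions are not taught in English, and the one field-language handout at hand already has the general wording. This stands as far as it goes: the documents do not show that any group receives the personal question. They do not rule it out either, because Hadiyisa is permitted and its source text is not named.

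Second, exercises are meant to help couples apply ideas to their own lives, and other items do so in both languages, such as the one on who takes household decisions. That is a legitimate design aim. It does not require couples to discuss violence in their own home in front of others.

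Third, Annex V follows a different session order from Table 2, where triggers come in session 2, so it is unclear where this exercise falls in the current plan. That is a further reason to settle the text. The manual's step lists put reflection on take-home work in every session from the second to the sixth.

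Two stronger readings are tempting and are not supported:

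- A reader might infer that an abused woman is forced either to disclose or to deny violence publicly, the more so because a session is repeated if couples answer fewer than 75% of the questions. No text requires an answer aloud; silence or a general answer remains open. The 75% rule is a comprehension check on the taught topic, separate from the reflection step.
- A reader might infer a calculable bias in the primary outcome in favour of the intervention. That would need a rate at which women switch to denial, which the documents do not give, and a base rate in the intervention arm, which depends on whether the 20% decline in section 6.8 is absolute (37.5 − 20 = 17.5%) or relative (37.5 × 0.8 = 30%). The direction is also open: teaching women to recognise violence could raise reporting, and the outcome is collected privately by female nurses, not by the health workers who teach.

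**Conclusion.** The point holds as a safety and consistency matter. The two handouts ask different first questions, the wording delivered is not fixed, and the personal version, followed by group reflection with husbands present, could expose an abused woman. Exposure is an inference from the set-up, not something the protocol prescribes. It rests on two assumptions: that a group could be taught from the personal wording, and that reflection with the couples takes place in the group session, as the manual's structure indicates.

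No numerical size can be attached. An effect on endline reporting is possible, but the documents fix neither its amount nor its direction, and the recommendation does not depend on it. The change is worth making because the possible harm is serious and the remedy costs almost nothing.

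**What to change.** - In Annex V, replace the first take-home item with the general question already used in Annex IX.
- Base any Hadiyisa text on that general wording, and make the language statements in the English and Amharic manuals agree.
- Add one line to the manual's section on take-home exercises and to the reflection step of the sessions: couples are not asked in the group to report violence in their own home.

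The cost is one replaced line, one added instruction and a check of the translations. Sample size, visit schedule and analysis are unaffected. The small downside is that the exercise becomes slightly less personal.
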